##### Parent’s health-related quality of life

The parent-reported 12-item Short-Form Health Survey (SF-12v2) [47] will be used. It is the most frequently used patient-reported outcome in clinical trials [48] and has been used most frequently in studies evaluating HRQOL of parents of CWE [19]. The SF-12v2 generates a physical and mental health summary score, and 8 subscales: physical functioning, role-physical, bodily pain, general health, vitality, social functioning, role emotional, mental health. The primary interest will be the mean mental and physical health summary score at the Immediate Follow-up (week 9), adjusting for the mean score at Baseline (week 0).

##### Children’s externalizing problems

Externalizing problems will be evaluated using the Externalizing Problems scale of the Behavior Assessment System for Children-Parent Rating Scale (BASC-3-PRS) [49]. This composite scale is composed of the following subscales: hyperactivelity, aggression, and conduct problems. We will utilize the BASC-3 preschool version (validated for children aged 2–5 years) and the BASC-3 child version (validated for children aged 6–11 years). Children with a *T*-score above 59 in a given scale are categorized as “at risk” for that domain. To ensure that parents complete the same version at each follow-up, and given that the study will last approximately 5 months (e.g., 20 weeks), children aged 5.792 years or older will be given the BASC-3 child version, and those aged less than 5.792 years will be given the preschool version at each follow-up. The primary interest will be the mean Externalizing Problems *T*-score at the Immediate Follow-up (week 9), adjusting for the mean score at Baseline (week 0).

##### Children’s internalizing problems

Internalizing problems will be evaluated using the BASC-3 Parent Rating Scale [49] Internalizing Problems scale. This composite scale is composed of the following subscales: anxiety, depression, and somatozation. Children with a *T*-score above 59 in a given scale are categorized as “at risk” for that domain. As explained above, parents of children aged 5.792 years or older will be given the BASC-3 child version, and those parents with children aged less than 5.792 years will be given the preschool version at each follow-up. The primary interest will be the mean Internalizing Problems *T*-score at the Immediate Follow-up (week 9), adjusting for the mean score at Baseline (week 0).

##### Children’s adaptive skills

Adaptive skills will be evaluated using the BASC-3 Parenting Rating Scale [49] composite Adaptive Skills scale. This composite scale is composed of the following subscales: adaptability, social skills, leadership, functional communication, and activities of daily living. Children with a *T*-score above 59 in a given scale are categorized as “at risk” for that domain. As explained above, parents of children aged 5.792 years or older will be given the BASC-3 child version, and parents of children aged less than 5.792 years will be given the preschool version at each follow-up. The primary interest will be the mean Adaptive Skills *T*-score at the Immediate Follow-up (week 9), adjusting for the mean score at Baseline (week 0).

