### Statistical methods

#### Statistical methods for primary and secondary outcomes {20a}

Descriptive statistics will be run with continuous variables summarized using means and standard deviations and categorical variables summarized using frequencies and proportions. To evaluate study feasibility, descriptive statistics will be used to summarize study procedures among all participants, including (a) number of families contacted, (b) participation rate, (c) reasons and/or barriers for non-participation, (d) attrition rate, (e) time to complete questionnaires, and (f) missing data on questionnaires. To evaluate (1) participant feedback and adherence to M3 and (2) intervention fidelity, data from the intervention and control arms will be combined and descriptive statistics used to describe responses to the Weekly Parent Questionnaire, Parent Pre-Post Assessment, and Child Pre-Post Assessment, M3 Adherence Checklist, and Quality of Implementation questionnaire.

To evaluate Efficacy Outcomes (e.g., HRQOL), we will use linear mixed models, which are suitable for group-administered interventions to account for the clustering in the intervention arm and no clustering in the control arm [63, 64]. The primary interest will be comparing the mean scores of the intervention and control arms at the Immediate Follow-up (e.g., HRQOL 1-week post-M3), adjusting for potential imbalance at Baseline (e.g., HRQOL pre-M3). Given that age group (younger vs. older) was a variable used in stratifying randomization, analyses will adjust for age group.

Similarly, generalized linear mixed models will be used to evaluate whether the intervention and control arms differ with respect to the proportion who show clinically significant improvement, and the proportion with clinically elevated symptoms post-intervention [65].

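### The BASC-3 Adaptive Skills rule sets 'at risk' at the high end of a scale of strengths, so the category labels the wrong children

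*Protocol article*

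**What the plan says.** The Outcomes section of the protocol article takes three BASC-3 composites from the parent rating scale and describes each by its subscales.

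- Externalizing Problems: "This composite scale is composed of the following subscales: hyperactivelity, aggression, and conduct problems".
- Internalizing Problems: "This composite scale is composed of the following subscales: anxiety, depression, and somatozation".
- Adaptive Skills: "adaptability, social skills, leadership, functional communication, and activities of daily living".

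All three get the same classification rule. For Adaptive Skills it reads that children with a T-score "above 59 in a given scale are categorized as" at risk for that domain. Nothing says that this composite is reverse-scored or that a low score is the favourable one.

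The main analysis of the outcome is on the continuous score: "The primary interest will be the mean Adaptive Skills" T-score at week 9, adjusted for baseline. In addition, the section on statistical methods for primary and secondary outcomes plans generalized linear mixed models comparing the arms on "the proportion who show clinically significant improvement, and the proportion with clinically elevated symptoms post-intervention".

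**The concern.** One upper-tail rule cannot mark risk both on scales that count problems and on a scale that counts skills, unless the skills scale is scored in reverse. The sentence appears to have been carried over from the two problem scales. Read literally, it puts a child with strong social and communication skills in the risk group and leaves out a child with very weak ones.

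The at-risk sentence is also the only cue to direction that the article gives for this scale. For the QOLCE-55 the article says outright that higher is better; for Adaptive Skills it does not. At stake are any proportion analysis that includes this scale, any description of how many children are at risk, and any subgrouping built on the label.

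**Working it through.** **1. Direction of each scale, from the article's own descriptions**

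| Composite | What the subscales measure | Adverse end | Stated rule | Consistent? |
|---|---|---|---|---|
| Externalizing Problems | problems | high | T above 59 | yes |
| Internalizing Problems | problems | high | T above 59 | yes |
| Adaptive Skills | competencies | low (inferred) | T above 59 | no |

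The cut-off is a definition, so there is no computed figure of the plan to reproduce.

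**2. Effect on a proportion**

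If a high score is good, a benefit shifts scores upward. An upward shift of any distribution cannot lower the proportion above a fixed high cut and cannot raise the proportion below a fixed low cut. The reversal therefore needs no assumption about mean, SD or normality; only its size does.

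**3. Illustrative size**

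Inputs:
- Stated cut: T above 59, from the article.
- Comparison cut: T below 41, the mirror image about 50. This is an assumption.
- T-scores normal, whole numbers, SD 10, starting mean 50 or 45. These are assumptions; the article gives no BASC-3 distribution.
- Benefit of 0.8 SD, that is 8 points. This is borrowed from the sample size section, where it refers to the QOLCE-55 (11.6 / 14.5 = 0.8).

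Formulas, with a half-point correction for whole-number scores:
- Written rule: P(T ≥ 60) = 1 − Φ((59.5 − μ)/10)
- Low-end rule: P(T ≤ 40) = Φ((40.5 − μ)/10)

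| Mean μ | Written rule | Low-end rule |
|---|---|---|
| 50 (start) | 1 − Φ(0.95) = 17.1% | Φ(−0.95) = 17.1% |
| 58 (after +8) | 1 − Φ(0.15) = 44.0% | Φ(−1.75) = 4.0% |
| 45 (start) | 1 − Φ(1.45) = 7.4% | Φ(−0.45) = 32.6% |
| 53 (after +8) | 1 − Φ(0.65) = 25.8% | Φ(−1.25) = 10.6% |

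**4. Sensitivity**

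Treating scores as continuous (cuts at exactly 59 and 41) and starting at 50:

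| Benefit | Written rule | Low-end rule |
|---|---|---|
| none | 18.4% | 18.4% |
| +3 | 27.4% | 11.5% |
| +5 | 34.5% | 8.1% |
| +8 | 46.0% | 4.5% |

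Starting at 40, a +5 shift moves the written rule from 2.9% to 8.1% and the low-end rule from 54.0% to 34.5%. At starting means of 40, 45 and 50 and shifts of +3, +5 and +8, the two rules always move in opposite directions.

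**The case against.** A reader might infer that a real benefit of M3 on adaptive skills would be reported as harm. The article does not support that. The primary interest for this outcome is the baseline-adjusted mean T-score, which uses no cut-off and remains numerically valid, provided that an increase is read as improvement.

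Nor does the article say that Adaptive Skills enters the proportion models. It speaks of "the proportion with clinically elevated symptoms post-intervention" without naming scales, and a skills composite is not naturally a symptom scale. Clinically significant improvement is not tied to the at-risk cut either; for the QOLCE-55 the article derives meaningful change from a minimum clinically important difference. The planned subgroup analysis concerns initial HRQOL and mental health problems and does not name adaptive skills. So the link from the wrong label to a reversed result is conditional.

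The size is also only illustrative. The 0.8 SD effect belongs to another instrument, and the rationale for eligibility itself warns that the broad criteria may limit the improvement seen. Finally, the scoring direction is inferred from names, because the article does not state it and the manual is not at hand.

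These objections limit the consequence and the severity. They do not rescue the sentence: it is a stated rule, it conflicts with the construct it is applied to, and nothing elsewhere in the article corrects it.

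**Conclusion.** The at-risk definition for Adaptive Skills is wrong as written, on the inference that a composite of strengths is scored with high as favourable. It flags the favourable tail and misses the unfavourable one. Any analysis, description or subgrouping that uses the category for this scale would run in the wrong direction. The size of the distortion depends on the assumed mean, SD, distribution and effect; the direction does not.

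The damage is contained. Adaptive skills is one of several secondary outcomes meant to give preliminary data in a pilot whose primary objective is feasibility. Feasibility, the sample size (built on the QOLCE-55) and the mean-score comparison are untouched. This should be fixed, but it does not threaten the trial's main conclusions.

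**What to change.** In the section on children's adaptive skills, state that higher Adaptive Skills T-scores are better, and define 'at risk' for the composite and its subscales at the low end. Take the cut-off from the scale manual, confirming the scoring direction at the same time; T below 41 is used above only as an illustration. If Adaptive Skills is to enter the proportion models, say so and code it in that direction.

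The cost is one sentence in the protocol and one line of scoring code. It is best done before outcome data are seen, because a cut-off changed afterwards looks data-driven.

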##### Children’s executive function

The parent-reported Behavior Rating Inventory of Executive Function (BRIEF) scale will be used to evaluate children’s self-regulation of cognition, emotion, and behavior [50]. We will utilize the BRIEF-2 version (validated for children aged 5–18 years) and the BRIEF-P (preschool) version (validated for children aged 2–6 years). These measures generate a global executive composite, cognitive regulation index, emotion regulation index, and behavior regulation index. Children with *T*-scores above 60 in a given scale are categorized as “at risk” for that domain. To ensure that parents complete the same version at each follow-up, children aged 5.00 years or older will be given the BRIEF-2, and those aged less than 5.00 years will be given the BRIEF-P version at each follow-up. The primary interest will be the mean global executive composite *T*-score at the Immediate Follow-up (week 9), adjusting for the mean score at Baseline (week 0).

##### Severity of children’s epilepsy

Parents will rate the severity of their child’s epilepsy using the Global Assessment of the Severity of Epilepsy (GASE), a single-item scale measured on a 7-point Likert-type scale [51, 52]. Seven additional items will be asked to validate parents’ response on the GASE; these questions will ask about the severity of seizures, intensity of seizures, falls or injuries during seizures, severity of period immediately after a seizure, amount of antiepileptic drugs, side effects of antiepileptic drugs, and interference of epilepsy or drugs with daily activities. At baseline only, the child’s neurologist will also complete the GASE and the additional seven items. Seizure frequency will also be rated by parents through two questions asking about the number of seizures and number of seizure-free days in the past 30 days. The primary interest will be the parent-reported mean GASE score at the Immediate Follow-up (week 9), adjusting for the mean score at Baseline (week 0).

##### Parent’s depression

The Center for Epidemiological Studies Depression, Revised Scale (CESD-R) is a widely used self-reported checklist evaluating level of depressive symptoms in adults [53, 54]. This 20-item measure generates an overall score for depressive symptoms, ranging from 0 to 60, with scores above 16 indicating risk for depression. The primary interest will be the mean depression score at the Immediate Follow-up (week 9), adjusting for the mean score at Baseline (week 0).

##### Parents’ anxiety

The 7-item Generalized Anxiety Disorder (GAD-7) scale evaluates parents’ self-reported symptoms of anxiety [55]. The GAD-7 generates an overall anxiety score ranging from 0 to 21, with scores above 10 indicating moderate-severe anxiety. The primary interest will be the mean anxiety score at the Immediate Follow-up (week 9), adjusting for the mean score at Baseline (week 0).

##### Parents’ stress

The Parenting Stress Index 4 Short-Form (PSI-4-SF) – screens for stress in the parent-child relationship, identifying dysfunctional parenting and child adjustment problems [56]. This 36-item parent-reported scale generates scores on three domains (Parental Distress, Parent-Child Dysfunctional Interaction, and Difficult Child), which combine to form a Total Stress scale. Scores in the 81st percentile or higher are indicative of high stress. The primary interest will be the mean Total Stress score at the Immediate Follow-up (Week 9), adjusting for the mean score at Baseline (week 0).

##### Sociodemographic and clinical characteristics

Parents will be asked to complete several questions on key demographic characteristics of the family (such as parents’ age, education, occupation, marital status) and children (such as gender, age, and comorbidities), similar to questions we have used successfully in previous studies [12]. Parents will also complete the Family Adaptability, Partnership, Growth, Affection, and Resolve (Family APGAR) [57, 58]. This scale evaluates satisfaction with family relationships in the following areas: coping with problems, partnership, growth, affection, and resolve; scores range from 0 to 10.

At baseline, neurologists will complete a short questionnaire documenting clinical characteristics of each patient’s epilepsy: severity of epilepsy, seizure type and frequency, type of epilepsy syndrome, age at onset and diagnosis, medication information, adverse effects, and other comorbid conditions. Type of seizure and epilepsy or epileptic syndrome will be classified using the International League Against Epilepsy’s 2017 classifications [59, 60].

##### Adverse events

At the start of each M3 session parents are asked whether they experienced any physical discomfort, emotional discomfort or distress, or an increase in problems in relationships with others, while practicing any of the M3 skills in the past week (see supplementary file). Parents are also asked if their child experienced any unwanted negative events while practicing any M3 skills in the past week.

##### Rationale for lack of child-reported measures

The majority of questionnaires will be completed by parents, with few exceptions (e.g., clinicians’ report on clinical characteristics, and children’s pre-post assessment of M3 skills). We acknowledge that children’s own perceptions are important and that this trial will not capture children’s perceptions of the intervention and its impact; however, we believe this is reasonable for three reasons. First and foremost, the primary objective of this pilot RCT is not to evaluate effectiveness as reported by children; the primary aim is to evaluate feasibility, focusing on participant adherence and facilitators’ adherence and quality of implementation. Second, questionnaires are completed at home and given the children’s age (4–10 years), parents would undoubtably have to provide the child with the questionnaires and likely assist, potentially biasing their responses. Lastly, given the children’s age (4–10 years), the choice of validated self-reported questionnaires is limited and it has been proposed that children under the age of 8 years may lack the cognitive maturity and verbal comprehension capacity to provide self-reports [61]. We are evaluating ways to best incorporate children’s self-reports in a subsequent large-scale RCT of M3.

##### Rationale for short follow-up period

A short follow-up period was chosen for two reasons. First, the primary objective of this pilot RCT is not to evaluate the long-term effectiveness of M3. Second, the short follow-up serves to minimize attrition in the control arm in two ways: by providing controls with the intervention as soon as possible, thereby keeping them interested and engaged in the study, and second it allowed for blinding of participants and facilitators to the study hypotheses, as described below, in section “Who will be blinded {17a}*”*. The intention is to evaluate longer term outcomes in a subsequent large-scale RCT.

#### Participant timeline {13}

Parents will be able to complete all questionnaires online via REDCap, or if preferred, using mailed questionnaires. The baseline and follow-up questionnaires are estimated to take 90 min to complete. Parents will also be asked to complete a brief online questionnaire via REDCap at the start and end of each M3 session pertaining to the content of the M3 sessions and their experience with the intervention.

Figure 1 highlights participants’ progression through the study. Two weeks prior to the first M3 session of the intervention arm, participants will be sent the baseline questionnaire and asked to complete it within 1 week, which will allow for a 1-week buffer window prior to the first M3 session for the intervention arm. Once the Baseline questionnaire is completed, participants will be randomized. One week after the last M3 session for the intervention arm, all participants will be sent the Immediate Follow-up questionnaire. Participants will be asked to complete the questionnaire within 1 week, with the goal of receiving all completed questionnaires within 2 weeks.

**Fig. 1 Fig1:**
[figure not shown]
Schematic of participant progress

Participants in the intervention arm will be asked to complete a similar questionnaire, the Extended Follow-up, 10 weeks after the end of the M3 session. For participants in the control arm, the Immediate Follow-up questionnaire is the final follow-up questionnaire they complete. To provide interested controls with the intervention as soon as possible, those interested in receiving the intervention will be placed in a queue and will be able to join the next scheduled M3 sessions. Therefore, M3 sessions may be composed of participants randomized to the intervention arm and/or controls who have completed the study (completed Baseline and Immediate Follow-up questionnaires). During the M3 sessions, all participants will complete the same online questionnaires pertaining to the content of the M3 sessions and their experience with the intervention. Once the intervention ends, those who were randomized to the control arm will not need to complete any follow-up questionnaires. Therefore, the role of the controls in the intervention would be to simply honor the commitment for everyone to receive the M3 sessions and to “fill” the group (given that 4–8 participants are needed per group). The advantage of including dyads randomized to intervention and dyads previously randomized to the control arm is that it will increase the pool of participants waiting to receive the intervention and thereby expedite the time it takes to fill each group. The other advantage is that it would ensure that dyads randomized to the control group will receive the intervention as soon as possible and ameliorate attrition in the control group.

#### Sample size {14}

The sample size calculation was based on the results of our pan-Canadian prospective cohort study of children (aged 4–12 years) with newly diagnosed epilepsy [45]. Two years after diagnosis, we observed the mean score on the QOLCE-55 to be 76.4 with a standard deviation of 14.5. To our knowledge, there are no estimates of minimal clinically important difference (MCID) for the QOLCE-55, and no intra-class coefficient estimates available for the impact of group-based psychological interventions in CWE. We therefore assumed a conservative ICC among participants in M3 of 0.10, an average cluster size of 6, and aimed to detect a large effect size (*d* = 0.8) [62], corresponding to a 11.6-point difference on the QOLCE-55 between the two study arms. The 11.6 point difference is in line with the MCID found for the adult equivalent HRQOL measure, the QOLIE-31 [44]. Using the method for a trial with a group-administered intervention, a control arm with independent subjects, and 1:1 randomization [63], the study requires 38 child-parent dyads in the intervention arm and 38 child-parent dyads in the control arm to have 80% power and the 2-sided 5% significance level. We will aim to recruit 100 child-parent dyads to account for a liberal estimate of 24% attrition.

#### Recruitment {15}

Participants will be recruited from the population of children treated for epilepsy in Southwestern Ontario by the Division of Pediatric Neurology, Children’s Hospital at London Health Sciences Center and the single pediatric neurology practice in Windsor, ON. The clinical neurology teams will identify all patients meeting clinical eligibility criteria and will provide their parents with a letter of information (LOI) that explains the aims of the study and all study procedures. The LOIs will be distributed by mail or occasionally in person during the child’s regularly scheduled epilepsy appointment for those patients due for an appointment in the near future. A member of the research team will subsequently contact parents in a few days to explain the study objectives and procedures, answer any questions, confirm eligibility, and obtain informed consent.

